### Study design

The study uses an Interrupted Time Series (ITS) Design [21, 22] with a duration of 15 months. All trials start in the control phase of randomized length with regular recruitment and change to the intervention phase with additional IT support, ensuring a minimum of one month in each phase and a minimum trial observation of 6 months. At least one month prior to the inclusion of *a* specific trial into the study, the length of the control phase for this trial is randomized centrally across all 10 sites. A block randomization was used to randomize the time of switching to the new scheme in the percentage of the planned enrollment time into the study. We used R version 4.1.2 and the package blockrand version 1.5 with the seed 9384902. We allowed for values between 0.15 and 0.85 with 0.05 steps, rounding the resulting time of switching to the first or 15th of a month. We generated 5 blocks with a size of 30 resulting in 150 ids. When a study was enrolled at one of the sites, the site contacted the independent person at Freiburg, who took the next free id from the randomization list and relayed the time of switching for the specific study. The persons responsible for enrollment had no access to the randomization list.

Due to the embedding of the intervention into and its overlap with the recruitment processes, it is practically not feasible to completely blind the study. Nevertheless, the randomized time point to switch to the intervention will only be disclosed to the sites 2 months before and only subsequently to the medical staff. The effectiveness will be measured by the number of recruited participants per trial and week standardized by the targeted number of participants to be recruited into the specific trial. This will be analyzed by means of a linear mixed model. In addition, user interviews will be conducted prior to the start of the intervention and at the end of the study. 

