**Fig. 2 Fig2:**
[figure not shown]
The basic flow of data from the electronic health records (EHRs) to the research repositories to the creation of patient recommendations in the screening list. Treatment data is recorded in the EHR as part of routine care (1), this data is regularly transformed to the OMOP CDM via ETL jobs (2). A query module (3) continuously scans the research repository for patients matching the defined trial eligibility criteria. If potential candidates are found, they are put on a web-based screening list (4), and a notification is sent via email. This notification is received by relevant practitioners or trial personnel (5) and the screening list can be accessed to further manually screen the suggested patients

Local recruitment staff decides over inclusion of individual patients based on the recruitment proposals on the screening list. Patient status, from recruitment proposal to inclusion, is documented in the screening list. Because it is based on pseudonymized research data, by default, this list displays only a pseudonymized medical record number, the year of birth, the gender, and the last known organizational unit within the hospital. This data can be used to either search the hospital information system with its applicable access controls, or the study personnel has to contact the attending physician based on the last known location of the patient. After consenting to disclose trial and personal data, the staff can then inform the patient about a possible participation in the trial. Some sites allow displaying the re-identified medical record number to make it easier to identify the patient. In these cases, re-identification works by technically integrating the screening list with the pseudonymization tooling established at the sites.

In the control phase, trial participants are recruited according to the respective standard procedure.

Termination criteria are not defined, since the interventional IT solution is used parallel to the conventional solution.

To increase the adherence of the recruiting staff, training courses are conducted and regular visits take place. Problems with adherence are logged.

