### Generation and implementation of allocation

Prior to the inclusion of *a specific* trial into the study, the length of the control phase for this trial is randomized centrally across all 10 sites. The overall observation period of the trials varies between 6 and 15 months. With a pseudo-random generator from the R-statistical package, the length of the control phase is randomly assigned to a value between 15% and 85% of the total observation period, which ensures that for short (6 months) trials control or intervention phases have at least a duration of one month. Respectively, a trial with an observation time of 15 months has control or intervention phases with a minimum length of 2.5 months. For each trial, an exact date for the start of the intervention phase is calculated from the inclusion date of the trial and the duration of the control phase.

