### Data collection

The following data is collected for each trial:

Trial specific parametersParticipating sitesRegistration information: unique trial identifier such as the ClinicalTrials.gov NCT number, the DRKS number, or the Universal Trial Number (UTN)Start of recruitmentPlanned and actual end of recruitmentExpected duration of recruitmentTargeted participant countExpected number of participants at each siteNumber of participants already recruited at the beginning of the studyTrial typeInclusion criteriaExclusion criteriaPersons (or groups) involved in recruitmentNumber of patients who were admitted to the site on a monthly basis as in- or outpatients

During the intervention:Number of screenings conductedNumber of recruited participants per weekNumber of recruitment proposals per week (automatically recorded by the IT-solution)Number of recruited participants not suggested by the system per week (i.e., only through standard recruitment procedures)

After the intervention:

Short interviews and surveys on the usability of the system are conducted with one user for each trial. To quantify the user experience and usability of the tool, the System Usability Scale (SUS) [25] and the User Experience Questionnaire - short (UEQ-S) [26] will be used.

Per recruitment proposal:

The following data is collected for each recruitment proposal. A suitable feedback mechanism for reporting trial inclusions must be established individually at the centers.Organizational unit of the site where the inclusion took place (automatically recorded by the IT system)Status as indicated in the recruitment list.“Recruitment Proposal”“Under consideration”“Does not meet eligibility criteria”“Is Participating in trial”“Not willing to participate”Outpatient or inpatient status at the time of inclusion

The patient inclusion data is primarily collected via the trial’s existing electronic documentation and transferred to custom data entry masks. To ensure the completeness of data collection, the documentarians from MIRACUM are in close exchange with the corresponding staff in the departments and trial personnel.

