### Statistical methods

The characteristics of the included studies will be presented in tabular form. All variables will be summarized using appropriate summary statistics. The mean, standard deviation, and the quantiles will be used for continuous variables and absolute and relative frequencies for categorical variables. If applicable, the variables will be visualized using boxplots and histograms, potentially over time.

The primary analysis will be conducted using linear mixed models with the actual recruitment number per week and trial standardized by the expected recruitment number per week and trial as the dependent variable. The choice is driven by the model’s ability to account both for fixed effects and random effects. This flexibility of this model is particularly suited for capturing the hierarchical structure in our data and aligns with the nature of the ITS design, where repeated measures over time and within-trial correlations are essential. A positive and statistically significant fixed effect of the binary variable “intervention allocation per week” will be interpreted as the measure for effectiveness. The corresponding effect will be evaluated for significance on the 5% level using the likelihood-ratio test. The model will be adjusted for trial, site, season, and time via random effects. Primarily, compound symmetry is considered as a working covariance matrix (constant correlation between time points), while autoregressive and unstructured covariance matrices are used as sensitive analysis. Additional sensitive analysis involves larger time frames, i.e., per month instead of per week, other distributions and link functions, i.e., generalized models, and classical statistics via mean values. Given the conservative sample size calculation based on a *t*-test, the linear mixed model is backed with adequate statistical power given the expected heterogeneous nature of the data.

To uncover further correlations and generate hypotheses, explorative analysis is carried out, including specific evaluation of site and trial characteristics.

No deviations from the protocol or missing data are expected. Trials are otherwise excluded from the primary analysis and their characteristics are compared to the other trials to identify potential problems for generalizability of the results.

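### The primary analysis drops whole trials for missing data or protocol deviations after randomization, and no named analysis puts them back

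*Protocol article*

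**What the plan says.** The rule is in the last paragraph of Statistical methods in the protocol article: "No deviations from the protocol or missing data are expected. Trials are otherwise excluded from the primary analysis". For the trials removed, "their characteristics are compared to the other trials to identify potential problems for generalizability of the results". The sensitivity analyses in the same section vary the working covariance, and then: "Additional sensitive analysis involves larger time frames, i.e., per month instead of per week, other distributions and link functions", with a comparison of mean values as a last option. All of these vary the model. None varies the set of trials.

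The design bears on what the rule does. Under Study design, "All trials start in the control phase of randomized length with regular recruitment and change to the intervention phase with additional IT support". Under Generation and implementation of allocation, "the length of the control phase is randomly assigned to a value between 15% and 85% of the total observation period", and "The overall observation period of the trials varies between 6 and 15 months". The effect of interest is the fixed effect of a weekly binary indicator of allocation in a linear mixed model. Study design and Blinding both accept that full blinding is not feasible. The Intervention section describes training and site visits to support adherence, and adds: "Problems with adherence are logged".

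**The concern.** This is a stated rule about the primary analysis set, not a detail left for an analysis plan. It removes the trial, not the affected weeks, and the triggers occur after the switch time has been randomized. The premise that none will occur sits badly with a protocol that trains staff for adherence, visits sites and keeps a log of problems over 6 to 15 months of weekly counts at ten hospitals.

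Two things are at stake. First, the primary estimate may no longer describe all randomized trials. If the trials removed are those where the tool was not used or not implemented as planned, the remaining set would tend to show the tool in a better light. Second, a trial with a gap loses its whole series, although a mixed model can be fitted to incomplete series.

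**Working it through.** **1. The plan's own figure.** Inputs from Sample size calculation: two-sided t-test, 5% level, 80% power, d=0.57, balanced, 100 trials. Solving the two-sample t-test gives 49.3 per group, so 50 per group and 100 in total. Power at 50 per group is 0.806 and the smallest detectable d is 0.566. The stated figure is reproduced.

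**2. Loss of whole trials on that basis.** The protocol gives no loss rate, so the fractions f are assumptions. Trials analysed = 100(1−f), split equally. Enrolment needed to keep 100 = 100/(1−f), rounded up.

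| f | trials analysed | power at d=0.57 | detectable d | enrolment to keep 100 |
|---|---|---|---|---|
| 0 | 100 | 0.806 | 0.566 | 100 |
| 5% | 95 | 0.785 | 0.581 | 106 |
| 10% | 90 | 0.762 | 0.597 | 112 |
| 20% | 80 | 0.711 | 0.634 | 125 |
| 30% | 70 | 0.652 | 0.679 | 143 |

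**3. How fast a one-missing-week rule bites.** An observation period of 6 to 15 months is about 26 to 65 weeks. Assume each week is missing independently with probability p. The share of trials with no missing week is then (1−p)^weeks.

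- p=0.5%: 0.995^26 = 0.878 and 0.995^65 = 0.722, so 12% of the shortest and 28% of the longest trials go.
- p=1%: 0.99^26 = 0.770 and 0.99^65 = 0.520, so 23% and 48% go.

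The longest series, which carry the most data, would be lost most often. Missing weeks that cluster in a few trials would cost fewer trials.

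**4. When exclusion biases the result.** The contrast within trials was simulated, as a simplification of the planned model. Settings, all assumed: 100 trials, 26–65 weeks, switch at 15–85% of the period, residual SD 1, SD 0.3 for each trial's own change after the switch, 2,000 runs per case.

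- *Exclusion depends only on the length of the intervention phase, true effect 0.* The estimate stays at about 0. Type I error after exclusion is 0.052, 0.054 and 0.047 with 5%, 10% and 20% of trials excluded.
- *Same mechanism, effect 0.2 in adhering trials and 0 in deviating ones.* All trials together give 0.191, 0.181 and 0.160; the reduced set gives about 0.20 each time. This is the ratio 1/(1−f): 1.05, 1.11 and 1.25.
- *Excluded trials are exactly those with the largest fall in recruitment after the switch, true effect 0.* The reduced set gives +0.032, +0.058 and +0.104, with type I error 0.10, 0.23 and 0.54. Keeping all trials gives about 0 and about 0.05. As a check at 10%, the mean of a normal variable with its lowest tenth cut off is 0.3 × 0.1755/0.9 = 0.0585.

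The third case is deliberately extreme. It shows the condition under which bias arises, not a forecast.

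**The case against.** The strongest reply is that the design protects itself. Only the switch time is randomized and every trial supplies both phases, so removing a trial removes its control and its intervention weeks together. The contrasts within the retained trials stand. That is right. A reader might infer that the rule breaks the randomization; what is lost is the set of trials and switch times as randomized, and the first simulation case shows no bias under no effect when exclusion follows phase length alone.

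A reader might also infer that the rule removes the trials where the tool failed. The text does not say so. The article does not define a deviation, which a fuller document may do, and logged adherence problems are not tied to exclusion. A tool that runs but adds no participants is neither a deviation nor missing data, so that trial stays in. Problems in the control phase would lead to exclusion too.

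Nor do the documents show that early closure triggers exclusion. The Primary outcome section relates recruitment to actual recruitment time, and the actual end is recorded.

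One sentence in Data collection might be read as a warning of missing outcome data: "A suitable feedback mechanism for reporting trial inclusions must be established individually at the centers". It belongs to the data on individual recruitment proposals. The same section takes inclusion data mainly from each trial's own electronic records, with documentation staff working towards completeness. Missing weekly counts may therefore be rare.

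Finally, the t-test is the protocol's simplified basis, which it regards as conservative. The protocol hopes to exceed 100 trials and prepared 150 randomization ids, more than the 112 or 125 in the table. That could offset lost power, though it is an aim and not a reserve, and it does nothing about selection. The planned comparison of characteristics makes exclusions visible but does not put outcomes back.

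**Conclusion.** The point holds in a limited form. The primary set need not be all randomized trials, it is decided by events after randomization in a study without full blinding, and no named analysis includes the trials removed. The rule can favour the tool by removing trials where it was not used or implemented as planned. An upward bias is possible but not established, and under no effect it needs a link between exclusion and the change in recruitment after the switch.

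The size is illustrative only. Losing 10% or 20% of 100 trials lowers power from 80.6% to 76.2% or 71.1% on the t-test basis and raises the detectable d from 0.57 to 0.60 or 0.63, if enrolment stops at 100. An estimate larger by 11% or 25% requires that every removed trial had no effect at all. The weekly missingness rates and the simulation settings are assumptions too. What does not depend on any assumed rate is that the rule discards observed weeks that the planned model could use.

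**What to change.** - Define the primary analysis as all randomized trials with observed weekly data. Code exposure by the randomized switch date, use every observed week in the mixed model under missing at random, and count weeks only up to the actual end of recruitment.
- Move the exclusion of deviating or incomplete trials to a per-protocol sensitivity analysis, with deviations defined in advance.
- Keep the planned comparison of characteristics.

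The cost is wording only; no new data are needed. The estimate may be somewhat smaller because non-adherent trials count. Power is recovered for trials that would have been lost to gaps in the data, but not where the tool had no effect: in the second simulation case, rejection with all trials kept was 0.979 against 0.988 at 10% deviating, and 0.941 against 0.972 at 20%. That is the price of an estimate that covers all randomized trials.

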### Data monitoring

A Data Monitoring Committee (DMC) is not used, as there can be no undesired effects of the intervention, since the IT-supported intervention tool is only used in addition to the standard method during trial recruitment.

A premature termination of the study is not planned.

### Risks and measures for error management

Since the intervention does not directly affect the patient, but is only used in addition to the standard recruitment procedure, no direct risks to patients are expected.

Patients who might be incorrectly proposed for trial inclusion will be recognized as such by the physician or trial assistant review and not included. This will happen as soon as possible with no additional burden for the patient.

A low risk may only result from the additional use of resources (personnel and time) when interacting with the recruitment support tool and the need for additional documentation.

Rather, we expect primarily positive effects for patients who otherwise would not have been identified as trial patients and could be proposed for inclusion due to the use of the application.

### Protocol amendments

Possible protocol extensions are formally added to the study protocol.

### Information and consent

Within the framework of the study, pseudonymized data are processed within the data protection laws of the individual sites and in the context of supporting medical care and research. The evaluation itself does not involve data from trial participants.

### Data protection and confidentiality

GDPR-conformaning privacy protection and data usage are guaranteed by an overarching central research program (BMBF Medical Informatics Initiative) and an overall consortial (MIRACUM) data protection concept. Data protection concepts are approved by the national conference of data protection officers and the data protection officers in the participating sites.

The complex process of identifying patients based on pseudonymized data using either the hospital information system or by contacting the treating physicians allows the system to be conformant with data protection regulations by relying on the access control mechanisms of the hospital information systems and established cooperation agreements between organizational units.

The study only collects the data listed under “Data collection.” The data is collected in a secure environment at each site.

### Access to data

The original data remain under the sovereignty of the respective locations. The data will be further processed according to the vote of the data protection, the ethics committee, and the Use & Access Committee. The aggregated results will be published and used jointly in the MIRACUM Consortium under the sovereignty of the MIRACUM Steering Board.

For statistical analysis, the collected data of each site is processed at one dedicated site within the consortium.

### Dissemination

The results are disseminated through publications at conferences and in specialist journals. The software components used in the intervention will be made freely available as open source, unless subject to further restrictions.

## Discussion

The evaluated IT solution is deployed on the common technical infrastructure of all partnering sites, leveraging international standards for interoperability. However, it is also deployed in a diverse setting of established organizational standards, tools, and processes. Therefore, user engagement is foundational to the success of the system. Ultimately, the implemented solution should benefit both trial personnel by reducing the manual effort required to identify eligible patients across large amounts of data and the patients themselves by providing them with access to promising treatment options within the trial.

## Data Availability

The developed software solution is publicly available under an open source license for download and usage at https://github.com/miracum/recruit.

## Abbreviations

EHR: Electronic health record
CDM: Common data model
ETL: Extract transform load
RCT: Randomized controlled trial
HL7: Health level 7
FHIR: Fast healthcare interoperability resources
OMOP: Observational medical outcomes partnership
HIS: Hospital information system
MIRACUM: Medical informatics in research and medicine
OHDSI: Observational health data sciences and informatics
DMC: Data Monitoring Committee
SUS: System usability scale
UEQ-S: User Experience Questionnaire - short
ITS: Interrupted time series
